#### Exclusion criteria

2.2.2

Patients with cardiovascular and cerebrovascular accidents (such as acute myocardial infarction, cerebral hemorrhage, and cerebral embolism) within the past 6 months.

Patients with severe heart failure symptoms or left ventricular ejection fraction <40%.

Patients with severe renal insufficiency requiring dialysis.

Patients with bleeding tendency, a history of active peptic ulcer, cerebral hemorrhage or subarachnoid hemorrhage, a history of stroke within the past 6 months, and contraindications to antiplatelet and anticoagulant therapy.

Patients with sick sinus syndrome, second-degree type I or third-degree atrioventricular block.

Unstable angina patients with resting angina attacks within 48 h.

Patients with a life expectancy <12 months.

Patients with significantly limited exercise capacity.

Patients with poor compliance who cannot complete the study as required.

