### Intervention measures

2.3

As an interventional trial, blinding of participants, treating physicians, and researchers directly involved in intervention implementation was not feasible due to the specific nature of the interventions (including oral SBP and exercise rehabilitation training), whose distinct characteristics would render blinding impractical. Importantly, outcome assessors responsible for data collection and statisticians conducting post-data-collection analyses remained blinded to group allocation throughout the study.

If a participant learns their group assignment during rehabilitation exercises, they will be assessed. If this knowledge could influence their behavior, they may be excluded from the study. Additionally, other participants will be monitored for information leaks. If others are affected, measures like re-evaluating data validity or exclusion from the study will be taken.

Tables 1–6 show the details content of the pre-exercise assessment, the three-phase exercise prescription, the exercise intensity grading, the type of exercise, the remote monitoring, and the outpatient period training program, respectively. The principles of full-cycle rehabilitation are shown in Figure 2. The schedule in this study is shown in Figure 3.

**Table 1 tab1:** Pre-exercise assessment.

Component	Detailed design
Cardiopulmonary function	CPET to measure VO_2_ peak and anaerobic threshold (AT)
Exercise risk stratification	AACVPR risk stratification criteria (incorporating LVEF, arrhythmia history)
Muscle function evaluation	30-s chair stand test, grip strength measurement
Psychological assessment	Hospital anxiety and depression scale (HADS)
Vascular evaluation	Coronary flow reserve (CFR), index of microcirculatory resistance (IMR, optional)

CPET, cardiopulmonary exercise test; AACVPR, American Association of Cardiovascular and Pulmonary Rehabilitation, LVEF, left ventricular ejection fraction.

**Table 2 tab2:** Three-phase exercise prescription.

Phase	Timeframe	Primary goals	Monitoring	Termination Criteria
Phase I	(Inpatient) 2–7 days post-PCI	Prevent deconditioning	Daily assessment	Chest pain > CCS Class II, SpO2 < 90%
Phase II	(Outpatient) 1–6 months post-discharge	Improve aerobic capacity	Weekly onsite + remote	ST depression ≥2 mm, SBP drop >10 mmHg
Phase III	(Home-based) 7–12 months	Long-term maintenance	Monthly follow-up	New-onset VT/AF

CCS, Canadian Cardiovascular Society, VT’AF, ventricular tachycardia/atrial fibrillation.

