**Table 3 tab3:** Based on CPET exercise intensity grading.

Intensity grading based on CPET	Target parameters	Applicable phases	Patient characteristics
Low intensity	40–50% of HR_peak_, RPE 11–12	Phase I/high-risk patients	LVEF < 45%, NYHA functional class II
Moderate intensity	60–70% of HR_peak_, RPE 13–14	Core of Phase II	No residual ischemia, ≥5 METs
High intensity	80–85% of HR_peak_, RPE 15–16	Optimization of Phase III	Young, low-risk, and well-adapted

RPE, rating of perceived exertion, LVEF, left ventricular ejection fraction NYHA, New York Heart Association; METs, metabolic equivalents.

**Table 4 tab4:** Type of exercise training.

Exercise modality	Details
Outdoor Aerobic training	Method: brisk walking Frequency: 3–5 times a week; duration: 30–45 min per session. Progression: increase the duration or intensity by 5% every month, or increase the walking distance and speed gradually according to your own situation.
Indoor Aerobic training	Method: Baduanjin Frequency: 3–4 times a week; duration: 12–26 min per session; take a 2-min break between each set. Precautions: perform the movements standardized, coordinate breathing with the movement rhythm, and avoid overexertion.
Flexibility training	Method: static stretching (30 s per muscle group) Focus: correcting the pectoralis major and minor muscles
Breathing training	Technique: 4–7-8 breathing technique Goal: reduce the oxygen consumption of the respiratory muscles and increase blood oxygen levels

Recorded videos of aerobic, resistance, flexibility, and breathing training will be uploaded to the WeChat for participants’ reference.

**Table 5 tab5:** Remote monitoring system.

Methods	Details
Equipment for measuring physiological indicators	Electronic blood pressure monitors
Monitoring platform	Custom APP features: - HR, resting BP, etc. upload - Exercise video upload

HR, heart rate, BP, blood pressure.

**Table 6 tab6:** Sample outpatient session (Phase II).

Time	Activity
8:00–8:30	Ambulatory BP monitoring + pre-exercise assessment (Borg scale)
8:30–8:45	Chest expansion and front raise exercise with heavy weights in hand (weight depends on the individual and increases over time)
8:45–9:30	Brisk walking: walk at a moderate speed for 30–45 min. Adjust the speed appropriately during the process to maintain the exercise intensity
9:40–10:10	Baduanjin: practice Baduanjin completely. Perform the movements standardized, coordinate breathing, and do 1–2 rounds, which takes about 12–26 min

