10:15–10:35	Breathing exercise: 4–7-8 breathing technique
10:35–10:50	Cool-down + post-exercise ECG monitoring

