Rehabilitation therapist	Possess practical qualification in exercise rehabilitation	a. Phase II rehabilitation: correct exercise postures, guide flexibility training and 4–7-8 breathing technique; b. Phase III rehabilitation support: record standardized exercise teaching videos and upload them to WeChat groups
Cardiovascular SPECIALIST	–	a. Safety control: complete exercise risk stratification for participants during enrollment and exclude high-risk patients; b. Emergency medical support: responsible for evaluation and handling of adverse events during follow-up; c. Medication education: provide patients with detailed medication education before they start taking SBP, including the dosage, frequency, time of administration, possible side effects, and the importance of adherence
Patient’s family	Voluntarily participate and receive training	a. Assist in supervision: remind patients to complete daily training as scheduled; Remind patients to take SBP on time every day according to the prescribed dosage and frequency; b. Emergency training: receive special training on CPR and be able to initially handle emergencies occurring during home-based exercise; c. Feedback communication: keep in touch with the research team (full-time research nurses) and feedback patients’ medication status (whether they take the medicine as required, any abnormal reactions) in a timely manner

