##### Exercise safety

2.5.2.1

Rehabilitation physicians will offer online and offline exercise guidance. Before starting, patients will receive a thorough assessment, including medical history, symptoms, physical exams, and tests. Physicians will advise on exercise precautions and joint protection for safety.

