##### Comprehensive safety

2.5.2.3

Before the study, patients will undergo a thorough assessment of cardiovascular, muscular, psychological, and vascular functions to identify risks. Personalized rehabilitation plans will be created from these evaluations, with strict control over the intensity and progress for high-risk patients. Facilities are equipped with first-aid equipment and medications, and medical staff are skilled in first-aid procedures.

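### The AV-block exclusion names second-degree type I and third-degree block but omits second-degree type II, probably a drafting or translation slip

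*Protocol article*

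**What the plan says.** The conduction-disease criterion in section 2.2.2 (Exclusion criteria) reads "Patients with sick sinus syndrome, second-degree type I or third-degree atrioventricular block". It is the only line in the article that mentions AV block, and it gives no reason for the grades chosen.

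Several other provisions bear on whether a patient with conduction disease would reach an exercise session:

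- Table 8 gives the cardiovascular specialist the task to "complete exercise risk stratification for participants during enrollment and exclude high-risk patients".
- Table 1 bases exercise risk stratification on "AACVPR risk stratification criteria (incorporating LVEF, arrhythmia history").
- Section 2.5.2.1 states: "Before starting, patients will receive a thorough assessment, including medical history, symptoms, physical exams, and tests".
- The sample Phase II session in Table 6 ends with "Cool-down + post-exercise ECG monitoring".
- Table 2 lists termination criteria by phase. The only one about rhythm is "New-onset VT/AF", in Phase III.
- Table 3 applies the low-intensity grade to "Phase I/high-risk patients", and section 2.5.2.3 promises individual plans "with strict control over the intensity and progress for high-risk patients".

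**The concern.** The criterion goes from second-degree type I straight to third-degree and skips the grade between them. Its evident purpose is to keep out patients with significant conduction disease, since it also names sick sinus syndrome and complete block. As printed it does not serve that purpose: a type I patient is refused and a type II patient is not, although type II is clinically the more serious second-degree form.

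What is at stake is safety and consistent screening. A type II patient could be enrolled and could be assigned to exercise. Whether that happens would depend on a general risk screen and not on the criterion written for conduction disease. The literal rule also refuses type I patients without explanation.

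**Working it through.** The plan states no figure on this point, so the check is a comparison of texts.

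**Step 1: read the criterion grade by grade.**

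| Condition | Excluded by the printed line? |
|---|---|
| Sick sinus syndrome | Yes |
| Second-degree AV block, type I | Yes |
| Second-degree AV block, type II | Not named |
| Third-degree AV block | Yes |

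**Step 2: look for another exclusion that covers type II.** The remaining criteria in section 2.2.2 concern recent cardiovascular or cerebrovascular events, severe heart failure or LVEF below 40%, dialysis, bleeding and antithrombotic contraindications, recent rest angina, life expectancy, limited exercise capacity and poor compliance. None addresses AV conduction.

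**Step 3: check the general screens.** The Table 8 duty, the Table 1 stratification and the assessment in section 2.5.2.1 could each bring a type II patient to notice. None states a rule for AV block. Finding the block does not tell staff whether the patient is eligible; the one line that should do so leaves this type out. The Table 8 duty is the strongest screen, but Table 3 and section 2.5.2.3 make provision for high-risk patients, so it is not clear that being high risk always means exclusion.

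**Step 4: check what would stop exercise once begun.** Table 2 has five termination criteria over three phases:

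1. chest pain (Phase I)
2. oxygen saturation (Phase I)
3. ST depression (Phase II)
4. blood-pressure drop (Phase II)
5. new-onset VT or AF (Phase III)

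None of the five names AV block or bradycardia. ECG monitoring appears in the sample Phase II session; Phase III is home-based with monthly follow-up.

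**Step 5: chance of exposure once enrolled.** Allocation is 1:1:1:1 (section 2.1), and the exercise and combined arms both train. A type II patient who passed screening would therefore have a 2/4 = 1/2 chance of an exercise arm. How many such patients would present cannot be derived from the article.

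**The case against.** The best case on the other side accepts the wording but disputes its consequence.

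- **The safeguards are substantial.** The Table 8 duty is stated outright and applies at enrolment. Cardiopulmonary exercise testing is part of the pre-exercise assessment (Table 1, section 2.3.2) and is repeated quarterly (section 2.5.4). Phase I has daily assessment, heart rate is uploaded through the app (Table 5), and nurses pass abnormal data to the rehabilitation physician (Table 8). This stands as a reason to rate the effect small. It does not repair the criterion, because none of these provisions names AV block.
- **The high-risk patients in Table 3 are a different group.** That row describes LVEF below 45% or NYHA class II, which, with LVEF below 40% excluded, points to mild impairment and not to advanced conduction disease. This is fair. Table 3 and section 2.5.2.3 leave the reach of the Table 8 exclusion unclear; they do not show that type II patients would be kept in.
- **Termination criteria do not decide eligibility, and a condensed table need not list every stopping reason.** This is also fair. The count in Table 2 shows only that the later safeguards, as published, do not make good the omission.
- **The article may shorten a fuller eligibility list.** That is possible, and the wording screening staff use is not known. But shortening does not readily explain keeping the grades on either side and dropping the one between them.
- **The ranking of type II above type I comes from outside the article.** That is correct. It is standard clinical classification, and the skipped grade is visible without it.

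**Conclusion.** The point holds. As printed, the criterion excludes second-degree type I and third-degree AV block and does not exclude second-degree type II, and nothing else in the article names type II. A drafting or translation slip is the probable explanation, but the article does not show which wording was intended.

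The size is small. Other screens make enrolment of such a patient less likely, no count of affected patients can be derived, and no sample size, endpoint or analysis figure is touched. The line should still be corrected, because it is an eligibility rule that protects safety in a trial with two exercise arms.

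The conclusion assumes the usual clinical ranking of the two second-degree types, and that the published line reflects the operative criterion. Confidence is medium, because the fuller eligibility list, if there is one, is not available.

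**What to change.** Amend the line in section 2.2.2 to one of these:

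- *sick sinus syndrome, second-degree type II or third-degree atrioventricular block*; or
- *sick sinus syndrome, second-degree (type I or type II) or third-degree atrioventricular block*, if type I is also meant to be excluded.

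The cardiology lead should confirm whether type I stays, and the wording used by screening staff should be made to match.

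Make the change promptly, and before further enrolment if enrolment has begun. The status is unclear: section 2.1 describes allocation in the past tense, while section 2.9 says pilot work to size the trial is still under way.

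The cost is an amendment to one line of the eligibility list. The effect on recruitment cannot be quantified from the article.

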### Intervention measures

2.3

As an interventional trial, blinding of participants, treating physicians, and researchers directly involved in intervention implementation was not feasible due to the specific nature of the interventions (including oral SBP and exercise rehabilitation training), whose distinct characteristics would render blinding impractical. Importantly, outcome assessors responsible for data collection and statisticians conducting post-data-collection analyses remained blinded to group allocation throughout the study.

If a participant learns their group assignment during rehabilitation exercises, they will be assessed. If this knowledge could influence their behavior, they may be excluded from the study. Additionally, other participants will be monitored for information leaks. If others are affected, measures like re-evaluating data validity or exclusion from the study will be taken.

Tables 1–6 show the details content of the pre-exercise assessment, the three-phase exercise prescription, the exercise intensity grading, the type of exercise, the remote monitoring, and the outpatient period training program, respectively. The principles of full-cycle rehabilitation are shown in Figure 2. The schedule in this study is shown in Figure 3.

**Table 1 tab1:** Pre-exercise assessment.

Component	Detailed design
Cardiopulmonary function	CPET to measure VO_2_ peak and anaerobic threshold (AT)
Exercise risk stratification	AACVPR risk stratification criteria (incorporating LVEF, arrhythmia history)
Muscle function evaluation	30-s chair stand test, grip strength measurement
Psychological assessment	Hospital anxiety and depression scale (HADS)
Vascular evaluation	Coronary flow reserve (CFR), index of microcirculatory resistance (IMR, optional)

CPET, cardiopulmonary exercise test; AACVPR, American Association of Cardiovascular and Pulmonary Rehabilitation, LVEF, left ventricular ejection fraction.

**Table 2 tab2:** Three-phase exercise prescription.

Phase	Timeframe	Primary goals	Monitoring	Termination Criteria
Phase I	(Inpatient) 2–7 days post-PCI	Prevent deconditioning	Daily assessment	Chest pain > CCS Class II, SpO2 < 90%
Phase II	(Outpatient) 1–6 months post-discharge	Improve aerobic capacity	Weekly onsite + remote	ST depression ≥2 mm, SBP drop >10 mmHg
Phase III	(Home-based) 7–12 months	Long-term maintenance	Monthly follow-up	New-onset VT/AF

CCS, Canadian Cardiovascular Society, VT’AF, ventricular tachycardia/atrial fibrillation.

**Table 3 tab3:** Based on CPET exercise intensity grading.

Intensity grading based on CPET	Target parameters	Applicable phases	Patient characteristics
Low intensity	40–50% of HR_peak_, RPE 11–12	Phase I/high-risk patients	LVEF < 45%, NYHA functional class II
Moderate intensity	60–70% of HR_peak_, RPE 13–14	Core of Phase II	No residual ischemia, ≥5 METs
High intensity	80–85% of HR_peak_, RPE 15–16	Optimization of Phase III	Young, low-risk, and well-adapted

RPE, rating of perceived exertion, LVEF, left ventricular ejection fraction NYHA, New York Heart Association; METs, metabolic equivalents.

**Table 4 tab4:** Type of exercise training.

Exercise modality	Details
Outdoor Aerobic training	Method: brisk walking Frequency: 3–5 times a week; duration: 30–45 min per session. Progression: increase the duration or intensity by 5% every month, or increase the walking distance and speed gradually according to your own situation.
Indoor Aerobic training	Method: Baduanjin Frequency: 3–4 times a week; duration: 12–26 min per session; take a 2-min break between each set. Precautions: perform the movements standardized, coordinate breathing with the movement rhythm, and avoid overexertion.
Flexibility training	Method: static stretching (30 s per muscle group) Focus: correcting the pectoralis major and minor muscles
Breathing training	Technique: 4–7-8 breathing technique Goal: reduce the oxygen consumption of the respiratory muscles and increase blood oxygen levels

Recorded videos of aerobic, resistance, flexibility, and breathing training will be uploaded to the WeChat for participants’ reference.

**Table 5 tab5:** Remote monitoring system.

Methods	Details
Equipment for measuring physiological indicators	Electronic blood pressure monitors
Monitoring platform	Custom APP features: - HR, resting BP, etc. upload - Exercise video upload

HR, heart rate, BP, blood pressure.

**Table 6 tab6:** Sample outpatient session (Phase II).

Time	Activity
8:00–8:30	Ambulatory BP monitoring + pre-exercise assessment (Borg scale)
8:30–8:45	Chest expansion and front raise exercise with heavy weights in hand (weight depends on the individual and increases over time)
8:45–9:30	Brisk walking: walk at a moderate speed for 30–45 min. Adjust the speed appropriately during the process to maintain the exercise intensity
9:40–10:10	Baduanjin: practice Baduanjin completely. Perform the movements standardized, coordinate breathing, and do 1–2 rounds, which takes about 12–26 min
10:15–10:35	Breathing exercise: 4–7-8 breathing technique
10:35–10:50	Cool-down + post-exercise ECG monitoring

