### Study design

2.1

This study is a prospective, single-center, randomized controlled clinical trial. Patients with CTO who underwent PCI in the cardiology department of our hospital. Using a computer-generated block randomization sequence (block size = 4), participants were allocated in a 1:1:1:1 ratio to one of four parallel groups: the SBP group, the exercise rehabilitation group, the combined SBP and exercise rehabilitation group, and the control group. Allocation concealment was ensured by a central randomisation module embedded in the Hospital Information System (HIS); the treatment assignment was automatically released only after the participant had been registered and baseline data entry was completed. Figure 1 shows the details of the study process. This study will strictly adhere to the Standard Protocol Items: Recommendations for Interventional Trials (SPIRIT) reporting standard (20).

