### Data collection and outcome measures

2.4

Eligible patients will be informed of the trial, agree to participate, and voluntarily sign the informed consent form. At the first visit, clinicians will collect basic clinical data of patients, including gender, age, medical history, and medication history. The next day, special personnel will measure patients’ height, weight, waist circumference, and resting blood pressure, and collect fasting venous blood for biochemical tests. In the data collection process, participants are assigned ID numbers, which are used as their identifiers in the system to safeguard their real identities. The collected information is stored in a highly secure database with strict access control, accessible only to the study leader and statistical experts. This ensures effective protection of participants’ privacy throughout the trial. Details of the outcome measures are shown in Table 7.

**Table 7 tab7:** Details of the outcome measures.

Outcome type	Specific content	Evaluation time	Evaluation method
Primary outcome	Evaluation of coronary microcirculation	Immediately and 1 year after revascularization	Myocardial contrast echocardiography (MCE): MBF; myocardial perfusion imaging (MPI): SDS
Secondary outcomes	Incidence of angina pectoris	1 month, 3 months, 6 months, and 12 months after revascularization	Clinical observation and recording
Secondary outcomes	Incidence of MACE during hospitalization, including all-cause death, recurrent myocardial infarction, and target lesion revascularization	Period of hospitalisation after revascularisation	Clinical observation and recording
Secondary outcomes	Incidence of 1-year MACE, including all-cause death, recurrent myocardial infarction, and target lesion revascularization	1 year after revascularization	Clinical observation and recording
Secondary outcomes	Assessment of quality of life improvement using SAQ	Period of outpatient review after discharge	Scoring with the validated Chinese version of the SAQ
Secondary outcomes	Inflammatory factors, angiogenesis-related factors, exercise-related factors	1 month, 3 months, 6 months, and 12 months after revascularization	Biochemical tests: IL-1, IL-6, and TNF; VEGF, Ang, NO, and eNOS; FSTL1 and FGF 21

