#### Patient compliance management

2.5.1

Patient compliance with SBP and exercise plans will be monitored via a follow-up platform and WeChat group, involving clinicians, rehabilitation physicians, patients, and families. Patients are required to upload daily exercise data. Nurses will communicate in-person with those who miss one or more times of follow-ups. Compliance is defined as logging in more than 3 days a week. The staffing arrangements for routine monitoring and follow-up are shown in Table 8.

**Table 8 tab8:** Regular follow-up and monitoring team.

Personnel category	Qualification requirements	Core responsibilities
Rehabilitation physician	Possess cardiovascular rehabilitation qualification	a. Develop personalized plans: determine exercise intensity (low/medium/high), exercise type (Baduanjin, brisk walking, etc.) and progress based on CPET; b. Provide technical guidance: responsible for on-site technical demonstration of Phase I rehabilitation and solving medical problems during exercise; c. Supervise safety: evaluate patients’ IMR based on rechecked CPET results every quarter to adjust exercise plans
Full-time research nurse	Hold cardiovascular specialist nurse certificate	a. Phase I rehabilitation: under the guidance of rehabilitation physicians, assist in on-site supervision of daily rehabilitation training; b. Remote follow-up: responsible for regular follow-up of patients 1–12 months after revascularization, including weekly telephone follow-up, receiving patients’ exercise data, and feeding back abnormal data to rehabilitation physicians; c. Compliance management: conduct targeted communication via phone calls, WeChat groups, etc. with patients who fail to complete exercise as required or miss data submission, analyze the reasons and provide solutions; d. Medication reminder: send medication reminders to patients through the research-WeChat groups at fixed times (7:00 a.m., 12:00 p.m., 7:00 p.m.) daily, and record whether patients take the medicine on time. e. Adherence intervention: for patients with poor medication adherence (such as missing doses frequently), communicate with them to find out the reasons (like forgetting, worrying about side effects) and provide targeted solutions.

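### The unqualified claim of blinded outcome assessors cannot hold for SAQ or patient-reported angina, and is unsupported for angina recording and the judged MACE components

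*Protocol article*

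**What the plan says.** Section 2.3 (Intervention measures) first says that "blinding of participants, treating physicians, and researchers directly involved in intervention implementation was not feasible". It then says that "outcome assessors responsible for data collection and statisticians conducting post-data-collection analyses remained blinded to group allocation throughout the study". No outcome is carved out of the second statement.

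Table 7 (section 2.4) lists the outcomes:

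- Primary: myocardial contrast echocardiography (MCE) and myocardial perfusion imaging (MPI).
- Angina at 1, 3, 6 and 12 months, and MACE in hospital and at 1 year: the method is "Clinical observation and recording". MACE is defined as "including all-cause death, recurrent myocardial infarction, and target lesion revascularization".
- SAQ during outpatient review: "Scoring with the validated Chinese version of the SAQ". The Discussion (section 3) describes it as reflecting how the patient subjectively feels.
- Biomarkers and safety outcomes: laboratory tests.

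Table 8 (section 2.5.1) is the only list of follow-up staff. The full-time research nurse helps supervise Phase I training, sends SBP reminders and records whether doses are taken. The same nurse is "responsible for regular follow-up of patients 1–12 months after revascularization, including weekly telephone follow-up". Section 2.5.3 mentions trained data collectors but does not say whether they are separate from the Table 8 team.

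**The concern.** Assessor blinding is the main protection against detection bias in a trial where patients and treating staff know the arm. Here the control group receives routine care (section 2.3.4), no placebo is described, and the active arms have more staff contact. Expectation can therefore shift what patients report, and knowledge of the arm can shift what staff record.

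The Background (section 1) hypothesises three benefits, and two of them are fewer MACE and better quality of life. Read with section 2.3, results on SAQ, angina and MACE would be taken as assessed blind. For SAQ that would be wrong. For angina and the judged parts of MACE it would rest on an assurance that the rest of the article does not back up. A difference produced by reporting or recording could then pass as a treatment effect.

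**Working it through.** The plan has no figure to reproduce, so the check sets the blinding statement in section 2.3 against each outcome in Table 7 and the roles in Table 8.

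| Outcome | Source of the information | Can the claim hold? |
|---|---|---|
| MCE, MPI (primary) | Image reader | Yes; nothing contradicts it |
| Biomarkers, safety tests | Laboratory assay | Yes; nothing contradicts it |
| SAQ | Patient, conceded to be unblinded | No, whoever scores the form |
| Angina: symptom report | Patient, conceded to be unblinded | No |
| Angina: recording | Recorder not named | Unsupported |
| MACE: all-cause death | Fact of death | Little room for judgement; not shown to be affected |
| MACE: recurrent MI, target lesion revascularization | Recorder not named; judgement involved | Unsupported |

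The unsupported entries follow in three steps:

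1. Table 7 gives a method for angina and MACE but no person.
2. The only follow-up team described is in Table 8, and no blinded assessor appears there.
3. The nurse responsible for months 1–12 knows the arm from exercise supervision and dose records. The angina visits at 1, 3, 6 and 12 months all fall in that window.

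**Illustration of possible size.** The article gives neither an angina rate nor a sample size (section 2.9 awaits pilot data). Every input below is therefore an assumption: a true angina rate of 0.30 in both arms, recorded at 0.27 or 0.24 in one active arm (10% or 20% relative under-recording), and 60 or 200 patients per arm.

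Let p̄ be the mean of the two recorded rates, SE = √(2·p̄(1−p̄)/n) and δ = difference/SE. The rejection probability of a two-sided 5% test is then approximately P(Z > 1.96 − δ) + P(Z < −1.96 − δ).

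| n per arm | Recorded rates | SE | δ | Rejection probability |
|---|---|---|---|---|
| 60 | 0.30 v 0.27 | 0.0824 | 0.364 | 0.0552 + 0.0101 = 6.5% |
| 60 | 0.30 v 0.24 | 0.0811 | 0.740 | 0.1113 + 0.0035 = 11.5% |
| 200 | 0.30 v 0.27 | 0.0451 | 0.665 | 0.0976 + 0.0043 = 10.2% |
| 200 | 0.30 v 0.24 | 0.0444 | 1.351 | 0.2714 + 0.0005 = 27.2% |

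With no under-recording the value is 5%. The table shows only that modest differential recording matters, and that it matters more in a larger trial. It is not evidence that such recording will occur here, and it says nothing about MACE or SAQ.

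**The case against.** The strongest reply is that section 2.3 and Table 8 can both be true. Table 8 sits under compliance management and assigns nobody to assess angina, MACE, SAQ or images. Section 2.5.3 refers to data collectors, who may be a separate group. A condensed article may leave the assessor of each outcome to the full protocol. Section 2.3 also discloses openly that patients are unblinded.

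Much of this stands, and it rules out several stronger readings that a reader might draw:

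- *Intervention staff record angina and MACE.* This is not stated. It is a plausible inference for angina from the nurse's follow-up role, and it is unproven for MACE.
- *Blinding is absent for most clinical outcomes.* The text contradicts the claim for SAQ and for the symptom report behind angina. Elsewhere it only fails to support it.
- *Adverse events are an outcome assessed unblinded.* The cardiovascular specialist who educates patients about SBP is indeed "responsible for evaluation and handling of adverse events during follow-up". But adverse events are not a Table 7 outcome; the safety outcomes there are laboratory tests.
- *Scan readers can see the arm because randomisation runs in the hospital information system.* Nothing says that allocation is visible to readers. Section 2.4 describes ID numbers and restricted database access.

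What the reply does not answer is the SAQ. A fuller document could name separate recorders for angina and MACE, but it could not make a questionnaire answered by unblinded patients a blinded assessment. The fault is an overbroad statement in the article, not a missing detail.

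**Conclusion.** The point holds in limited form. The blinding statement in section 2.3 is wrong as applied to SAQ and to the patient's report of angina. It is unsupported for the recording of angina and for the classification of recurrent MI and target lesion revascularization. The documents do not say who records these events.

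Only secondary outcomes are touched, although they include two of the three hypothesised benefits. The primary imaging outcome, the laboratory outcomes and all-cause death are not shown to be affected. The size of any bias cannot be derived from the article, and the illustrative range rests wholly on an assumed rate, direction and degree of bias, and arm size. The statement should be corrected; the point does not threaten the primary analysis.

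**What to change.** 1. In section 2.3, restrict the blinding statement to MCE/MPI reading, laboratory assays and the statisticians.
2. Describe SAQ and angina as open-label, patient-reported outcomes wherever results are claimed.
3. State that the angina records at 1, 3, 6 and 12 months, the SAQ forms, and the classification of MI and revascularization are completed by existing data collectors (section 2.5.3) who perform no Table 8 intervention task.

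Items 2 and 3 do not conflict. Separate collectors reduce bias from the recorder, and the open-label description remains necessary because the patient still knows the arm.

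The cost is a less favourable blinding claim and some reassignment of existing roles. The article does not say how many data collectors there are or whether they are free at those visits, so the sponsor should confirm this. No patients, visits or procedures are added.
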